Therefore, based on the evidence, the specific objectives of the study are: To examine the (a) cardiorespiratory fitness, (b) skeletal muscle structural and functional, (c) inflammatory, (d) bone health, and (e) nutritional intake parameters.To determine the effects of aging and the physical activity level on the measured parameters.To describe the relationship between the ageing and physical activity level with monitored parameters.To identify the health benefits, and possible negative effects, of lifelong one-sided endurance training.

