### 2.3. Sample Size

Based on the pilot study, with a mean effect size and a power of 0.9, the sample size of 14 participants per group would be needed to obtain a significant result. However, we will hire 20 subjects per group (in total, 80 subjects) to eliminate potential risks of drop out on the study outcomes. Sample size was calculated using G * Power 3.1.9.2 software.

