### 2.4. Subjects

The study will involve a total of 80 healthy male subjects divided into four groups (n = 80): group 1, endurance-trained runner athletes (young athletes—YA; n = 20, age range 20–30 years); group 2, adults less active than recommended (young sedentary—YS; n = 20, age range 20–30 years), group 3, master endurance running athletes (master athletes—MA; n = 20, age range 65–75 years); group 4, seniors less active than recommended (elderly sedentary—ES; n = 20, age range 65–75 years, respectively). The groups of young and master endurance-trained runner athletes will only consist of the active marathon runners.

Subjects must meet the following inclusion criteria to participate in this study:(a)for athletes’ groups:
defined as more than 300 min per week of running activity which is, by ACSM [8], considered as vigorous intensity of endurance activity.Both groups must regularly participate in running competitions (in 10 km, half, and full marathon) for young athletes for at least 3 years and for master athletes for at least 25 years.Have a personal best on 10 km run in last season under 35 min in YA group and under 55 min in MA.(b)for groups less active than recommended: no history of regular physical activity training and no more practice than 150 min of moderate or 75 min of vigorous intensity per week.

The standard inclusion criterion for every group will be body mass index (BMI) (range 18.5–30 kg/m^2^).

Exclusion criteria will be recent or current infection, physical disabilities, malignant disease, cardiovascular, metabolic, autoimmune diseases, malnutrition, and pharmacological interference (e.g., steroids, nonsteroidal anti-inflammatory agents, immunosuppressive and antineoplastic drugs). Moreover, the use of performance-enhancing drugs in the past and during the study period is exclusionary.

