### 4.8. Data Analysis and Management

All collected data will be cleaned, coded, and entered into the computer. The anonymized data will be uploaded to a cloud server for storage. Access to this data store will be password protected. The data collected from the study will be stored on faculty One-drive cloud servers. After data collection, data from the entire study will be retrieved from the One-drive and downloaded as an Excel file (Microsoft Office, Redmond, WA, USA). Data analysis will be performed using the SPSS 23 (IBM, New York, NY, USA).

The descriptive parameters will be reported as mean values ± standard deviations (SD) and 95% of the confidence interval (95% CI). Data will be assessed for normality and homogeneity to ensure that the analysis’ assumptions will be met, using the Shapiro–Wilk test, Levene’s test, visual check of histograms, and Q–Q plots.

A one-way ANOVA with Bonferroni post hoc correction will be used to determine differences between the groups in all measured parameters. Additionally, Cohen’s d effect size (ES) will be used to calculate between-group differences and will be interpreted using the following thresholds: 0–0.2 was trivial, 0.2–0.6 small, 0.6–1.2 moderate, 1.2–2.0 large, 2.0–4.0 very large, and >4.0 extremely large effect [42].

Association analyses will be performed using the Pearson product–moment correlation coefficient. The strength of the relationship was determined using the following criteria: 0.1, small; 0.3, moderate; 0.5, large; 0.7, very large; 0.9, nearly perfect > 0.9 [43].

The results will be considered significant for values of <0.05.

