## 6. Conclusions

In the present study, we will focus on revealing the positive effects and potential negative risks associated with lifelong physical activity beyond and under the recommendations defined by WHO. By using a wide range of diagnostic procedures, we gain a unique opportunity to comprehensively assess the impact of lifelong physical activity on the human body and contribute to expanding the knowledge base in the field. In addition to evaluating the current state, we assume the discovery of several relationships between diagnosed parameters, which will allow us to explain and describe the mechanisms responsible for changes occurring in the human body.

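### An unadjusted Pearson correlation across four groups chosen at opposite ends of age and activity cannot support relationships or mechanisms between parameters

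*Protocol article*

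**What the plan says.** The protocol article covers all association analysis in one sentence of section 4.8: "Association analyses will be performed using the Pearson product–moment correlation coefficient". Strength labels running from 0.1 to 0.9 follow, and then the criterion "The results will be considered significant for values of <0.05". The section does not say whether r is computed over all 80 men or within each group. It names no adjustment for group, age or activity.

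Section 2.4 defines the sample. The young groups are aged 20–30 ("young athletes—YA; n = 20, age range 20–30 years") and the older groups 65–75 ("master athletes—MA; n = 20, age range 65–75 years"), with 20 men in each of the four groups and nobody aged 31 to 64. Athletes run more than 300 minutes a week. The comparison groups have no training history and stay within 150 minutes of moderate or 75 minutes of vigorous activity.

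Two passages show what the associations are for. The third specific objective in the Introduction is "To describe the relationship between the ageing and physical activity level with monitored parameters". Section 6 goes further: "we assume the discovery of several relationships between diagnosed parameters, which will allow us to explain and describe the mechanisms responsible".

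**The concern.** A Pearson r computed over separated groups adds the covariance of the group means to the covariance within groups. Two parameters that both rise with training, or both fall with age, will then correlate across the whole sample even if a man's value on one says nothing about his value on the other once his group is known.

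The one-way ANOVA already reports those group differences. Expressing them again as a correlation between two parameters adds no evidence that the parameters are linked. If such correlations are then used to explain mechanisms, as section 6 expects, a shared dependence on age or training is presented as a link between the parameters themselves. The sign can also come out wrong, as the working shows.

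**Working it through.** The protocol gives no figure for the correlation analysis, so there is none to reproduce. The check asks what pooled r would show if two parameters were unrelated within every group.

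**Inputs from the documents**
- Four groups of 20, N = 80 (sections 2.3 and 2.4).
- Significance at 0.05 (section 4.8); two-sided is assumed.
- Section 4.8 calls a difference of 1.2 to 2.0 SD large. This serves as a guide to plausible separations.

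**Assumptions**
- Normal data, within-group SD 1, within-group correlation 0.
- Separation d, in SD, between the levels of an axis (young or old; trained or sedentary). The protocol gives no pilot means or SDs, so d is varied.

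**Formula.** Let V be the variance of the four group means (divisor 4) and C the covariance of the two parameters' group means. Then pooled r = C / √[(1 + V_X)(1 + V_Y)]. If both parameters have the same pattern of means, this becomes V / (1 + V).

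- *Both parameters shift on both axes:* group means are d × (1, 0, 0, −1), so V = d²/2.
- *Both shift with activity only:* group means are ±d/2, so V = d²/4.
- *One shifts with age only, the other with activity only:* the four cross-products cancel, so C = 0 and r = 0.
- *Same direction on activity, opposite on age:* C = d²/4 − d²/4 = 0, so r = 0.

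The share of studies with p<0.05 comes from 20,000 simulated studies per scenario.

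| Pattern | d | V | Pooled r | p<0.05 |
|---|---|---|---|---|
| Both axes | 0.6 | 0.18 | 0.18/1.18 = 0.15 | 28% |
| Both axes | 0.8 | 0.32 | 0.32/1.32 = 0.24 | about 60% |
| Both axes | 1.2 | 0.72 | 0.72/1.72 = 0.42 | 99% |
| Both axes | 2.0 | 2.00 | 2.00/3.00 = 0.67 | 100% |
| Activity only | 0.6 | 0.09 | 0.09/1.09 = 0.08 | 11% |
| Activity only | 1.2 | 0.36 | 0.36/1.36 = 0.27 (0.265 before rounding) | about 69% |
| Activity only | 2.0 | 1.00 | 1.00/2.00 = 0.50 | 100% |
| One age only, other activity only | 0.6 to 4.0 | – | 0 | 5% or less |

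**An anchor from the plan's own sample size.** Section 2.3 states 14 per group at power 0.9 and gives no number for the effect size. If the test was the four-group ANOVA at 0.05, this implies f of about 0.52, where f² plays the part of V. Two parameters with that spread and aligned means give r = 0.273/1.273 = 0.21, significant in 49% of studies at N = 80.

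**Sign.** Take a true within-group correlation of −0.30 and shifts of 1.2 SD on both axes. Pooled r is then (0.72 − 0.30)/1.72 = +0.24.

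**After adjustment for group.** With 80 − 4 − 1 = 75 degrees of freedom, the mean r is 0.00 and the share with p<0.05 is 4.7% to 5.3% in every scenario with zero within-group correlation. The critical |r| is about 0.22, against 0.220 for the pooled r. A separate correlation in one group of 20 needs |r| of at least 0.444.

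**The case against.** The strongest reply is that section 4.8 does not mention pooling. Correlations within each group would be free of this artefact, and a condensed article may leave the analysis set to a fuller document. It is true that pooling is inferred. However, the article does fix the method, the strength labels and the significance level, and one unstratified coefficient is naturally read as covering the whole sample. For age, a within-group r cannot serve the objective. For activity, the need to pool is less clear, because the accelerometer data of section 4.4 can vary within a group.

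A second reply is that the pooled correlation in this mixed sample really is non-zero, so a significant result is not an error about that sample. This also stands. The error enters only when the coefficient is read as a link between parameters. The sentence in section 6 that invites this reading does not mention Pearson, but section 4.8 offers no other method for associations.

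A third reply is that the largest figures come from the most favourable alignment. That is correct: activity-only shifts inflate less, and some patterns do not inflate at all.

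A reader might also infer that the third objective rests on false positives. The documents do not support this. If a parameter truly differs with age, its correlation with age restates a real contrast. Nor can the strength labels be faulted for assuming a particular kind of sample, since that depends on a cited source that is not shown.

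**Conclusion.** The concern holds for correlations between parameters whose group means line up on age, training or both. At separations that section 4.8 itself calls large (1.2 to 2.0 SD), pooled r would be about 0.27 to 0.67 with no within-group relationship at all, and about 69% to 100% of studies would declare it significant. At 0.6 SD the share is 11% to 28%.

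These figures rest on two things that the documents do not state: that r is pooled over the four groups, and the assumed separations. A reader might infer that nearly every reported correlation will be spurious. The calculation does not show that, because near-certain significance needs large and aligned group differences in both parameters.

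This should be fixed, but it does not threaten the study's main result. The primary comparison of VO2peak, and the other group comparisons, use ANOVA and are untouched. What is at risk is the interpretation of relationships between parameters as mechanisms.

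**What to change.** In section 4.8:

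- State the analysis set for each kind of association.
- For relationships between parameters, use partial correlation adjusted for group, or a linear model with group as a factor. Give group-specific coefficients with confidence intervals as support.
- Label any pooled r as a description of the mixed sample, and do not read it as mechanism in the conclusions.
- Report the effects of age group and activity group as group mean differences with confidence intervals.

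This needs no new data: only a change of wording and a little more analysis. The threshold for significance hardly moves. Significant correlations will be fewer and smaller, and the group-specific coefficients will be imprecise at 20 men per group. Group adjustment also removes the between-group variation of interest in the age and activity objective, which is why those effects should be reported separately as mean differences.

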## 5. Discussion

Physical fitness and the level of physical activity play an important role in maintaining health and reducing the negative effects of aging on the human body. Most of the positive effects are due to the implementation of the volume and intensity of physical activities recommended by the WHO [5]. However, the WHO recommendations suggest that increasing the training volume and intensity beyond the recommended range may increase the positive effects on the body and also reduce the negative impact of aging. Nonetheless, no upper limit has been exactly set, and limited numbers of studies have been done to uncover the positive and negative aspects of the volume of preferred physical activity, especially in older adults. On the contrary, a combination of a high volume and intensity of physical activity may possibly not only have health benefits, but also may have a negative impact on body composition, the musculoskeletal system, and others [14,44].

Consequently, the study might have several practical implications for coaches, both master, and young marathon runners, as well as for clinical practitioners and dietitians. The natural decline in the endurance exercise performance of master runners is present due to a lower training volume as well as age-related physiological changes compared to their younger counterparts. However, these changes have been so far poorly explained in the literature from the point of view of the complexity and interactions of human body systems on different levels. Thus, the study may bring new insides and explanations. Furthermore, to our knowledge, relative energetic deficiency is common among endurance runners. Thus, the investigations of the RED syndrome and its effect on the physiological aspect and exercise performance, not only in young endurance runners, but throughout the lifespan of master runners, might be valuable, especially for medical practitioners, and clinical and sports dietitians.

## 6. Conclusions

In the present study, we will focus on revealing the positive effects and potential negative risks associated with lifelong physical activity beyond and under the recommendations defined by WHO. By using a wide range of diagnostic procedures, we gain a unique opportunity to comprehensively assess the impact of lifelong physical activity on the human body and contribute to expanding the knowledge base in the field. In addition to evaluating the current state, we assume the discovery of several relationships between diagnosed parameters, which will allow us to explain and describe the mechanisms responsible for changes occurring in the human body.

## Figures and Tables

**Figure 1 ijerph-19-13184-f001:**
[figure not shown]
Data Collection Scheme per subject. Created with BioRender.com.

## Data Availability

The datasets analyzed during the current study are available from the corresponding author upon reasonable request.
